### Hypothesis and aims of the trial

Our overarching hypothesis is that IL-1 mediated pathways drive hyperinflammation and severe disease in dengue. We hypothesize that therapeutic IL-1R blockade in selected patients with dengue will improve clinical outcomes through attenuation of the inflammatory responses.

This phase II randomized controlled trial primarily aims to assess the impact of anakinra on clinical outcomes in dengue patients with hyperinflammation. The accompanying immunological and transcriptomic analyses aim to identify novel mechanisms and pathways that may represent future biomarkers and therapeutic targets.

## Methods

### Design

This is a double-blinded randomized placebo-controlled phase II trial of anakinra in patients diagnosed as having dengue with warning signs/severe dengue and hyperferritinaemia (>2000 ng/ml) (
Figure 1). The study will enrol 160 adults and children ≥ 12 years old admitted to the Hospital for Tropical Diseases, Ho Chi Minh City. Participants will be randomized 1:1 (anakinra:placebo) on electronic database system (Ennov) and stratified according to the ward of recruitment (Intensive Care Units/Emergency Department or the general dengue wards). Patients with warning signs or severe dengue (defined by 2009 WHO classification) and ferritin > 2000 ng/ml will be eligible for enrolment.

**Figure 1. f1:**
[figure not shown]
Trial flowchart.

Intravenous (IV) anakinra (200 mg twice daily) or visually matched placebo (0.9 % normal saline) will be given for 4 days.

### Inclusion and exclusion criteria

Patients will be eligible for study enrolment if they: (i) are more than or equal to 12 years of age; (ii) have a clinical diagnosis of dengue and at least one warning sign or severe dengue (based on the World Health Organization (WHO) 2009 or Vietnamese Ministry Of Health (MOH) – Dengue guidelines)
^
23,
24
^; (iii) have plasma ferritin levels > 2000 ng/mL ; (iv) agree to come back for two follow up visits between day 30 – 35 and at around day 90 afterillness onset; and (v) provide written informed consent.

Exclusion criteria include: (i) pregnancy (confirmed by either clinical examination or urine dipstick for human chorionic gonadotropin hormone); (ii) localizing features suggestive of an alternative diagnosis; (iii) taking immunosuppressive drugs or other biologics in the last month; (iv) underlying malignancy or immunosuppression; (v) children less than 12 years of age; (vi) have baseline GFR < 30 ml/min; (vii) having a neutrophil count < 1.0 × 10
^9^/L; (viii) being treated for tuberculosis; (ix) HBsAg-positive; (x) taking any drug with significant interaction with anakinra (concomitant medication and drug interactions); (xi) patients who are considered unlikely to attend follow-up visits because of long travelling distance to the study clinic or other reasons.

### Primary endpoint

The primary endpoint of this study is the delta mSOFA score* (change in mSOFA score over 4 days after randomization).

*mSOFA = modified Sequential Organ Failure Assessment score (modified for resource limited settings and dengue) see Appendix 1 for score.

### Secondary endpoints

The secondary endpoints are: 30-day mortality; change in mSOFA score at day 7 post randomization; number of days in ICU; number of days in hospital; number of individuals with serious adverse events (time-period 1–5 days and 6–30 days); number of adverse events per individual during the whole study course; change in ALT and platelets over 5 days following randomization; change in ferritin and CRP levels over 5 days following randomization and until day 30 after illness onset; time to normalization of platelets (defined as >150 ×10
^9^/l) and neutrophils (>2 ×10
^9^/l); platelet nadir; fever clearance time (defined as <37.5 °C for at least 48 hours; measured 4 times/day); duration of viraemia (number of days to first negative qPCR and NS1); AUC viraemia (from enrolment to negative); EQ-5D-5L questionnaire score at hospital discharge and day 30.

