### Study treatment, monitoring and follow-ups

Subsequent study procedures includes: daily study drug administration, daily clinical assessment, case Record Form (CRF) completion and blood sampling for a full blood count, biochemistry including ferritin, diagnostics, other inflammatory and vascular biomarkers and RNA extraction.

Participants will receive study treatment with Anakinra (Kineret) or visually matched placebo, given intravenously 200mg twice a day for 4 days (or 2mg/kg IV BD in children). Other general management of the febrile episode will be at the discretion of the treating physicians.

Study drugs will be stored in a refrigerator in a secure location at 2°C to 8°C and protected from light. All medication storage and administration will be regulated through the central pharmacy of the hospital to ensure good quality and control of medication handling. For the purpose of ambulatory use, Kineret may be kept at room temperature up to 25°C for a maximum of 72 hours.

All patients will be asked to come back for follow-up visits at day 30 and day 90 after fever onset. At these times, research blood samples will be taken for convalescent serology, immunology studies, a full blood count and biochemistry tests. Patients will be contacted 3 – 5 days prior to the follow-up visit to arrange an appropriate appointment date and time. Any patient who misses the follow-up visit will be contacted by phone either to reschedule the visit or to collect information if patients are unable to return in-person. 

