### Safety review and monitoring

The trial will be conducted in two phases. The initial pilot phase (cohort 1) includes 10 adults (≥ 16 years old) who will be recruited and monitored closely sequentially during the study course. Each patient will be administered either anakinra or placebo for 4 days (5 anakinra, 5 placebo).

A Data Monitoring Committee (DMC) review will take place when day 5 data are available from the first 10 patients enrolled. Based on a review of all reported serious adverse events and overall clinical outcomes, the DMC will recommend continuation, amendment of the protocol or stopping the study. Following satisfactory safety review after the 10
^th^ patient, the study will advance to the next phase to enrol the remaining 150 patients. The DMC will continue performing interim reviews after every 50 recruited patients to evaluate safety and tolerability of the study drug. In the event that any unusual or unpredictable serious adverse event occurs, the study team will temporarily pause recruitment and report data to local ethics committees for review.

The study drug will be stopped for an individual if they (1) request drug discontinuation ; (2) develop any AEs which require discontinuation of the study medication, including severe hypersensitivity reaction, severe acute renal impairment (eGFR below 30mL/min/1.73m
^2^), severe neutropenia (absolute neutrophil count < 0.5 × 10
^9^/L for at least 2 consecutive days [24 ± 6 hours]).

All AEs occurring during the trial will be recorded in the CRF regardless of their relativity with trial medication and will be reported to OxTREC in the annual review form, to the DMC in accordance with the DMC charter and to local ECs following local regulations. Clinical and Laboratory events will be graded according to Common Terminology Criteria for Adverse Events (CTCAE) definitions.

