### Data collection

Study data will be collected using an electronic CRF, except identification information which will only be recorded on paper CRF. All patients will be reviewed daily until discharge. Standardized clinical information and a full blood count, biochemistry and research blood sampling will be performed at each visit, plus any other tests deemed necessary by the attending physician. Details of all adverse events will be recorded on specific forms. An ultrasound scan of the chest and abdomen to assess vascular leakage will also be performed on alternate days in all participants by a study staff member using the portable ultrasound scan machine provided by OUCRU.

During the follow-up visits at day 30 and 3-months after the fever onset, patients will be asked about any newly emerging or persisting symptoms using a standardized questionnaire. Research blood samples will be taken for convalescent serology, immunology studies, full blood count and biochemistry tests.

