### Statistical considerations

**
*Sample size.*
** Given that delta mSOFA score has an approximately normal distribution
^
25
^ with a standard deviation of 2.4, which was based on a cohort of 38 adults admitted with severe dengue, we would need a sample size of 80 patients per group to detect a between-group difference of at least 1.0 point with 80% power and 5% type-I error rate.

**
*Statistical analysis.*
** The primary endpoint (delta mSOFA score) and the secondary endpoints (ALT, CRP, PLTs and ferritin) will be analyzed using a linear mixed-effects model, which models their values over the first 4 days for mSOFA and 5 days for lab tests (as specified in sections 2.4.1 and 2.4.2). We will use a linear trend for time as fixed and random effects. The slope of this model reflects the change in value over time. Therefore, the effect of anakinra is measured as the difference in slope between treatment groups. This difference will be assessed via the interaction between time and treatment group in that model, and presented with a corresponding 95% confidence interval. For the change at day 30 (ferritin and CRP) we will use the difference with the value at randomisation. Mortality will be assessed by comparing Kaplan-Meier curves via log-rank test. The number of serious adverse events will be compared via 2×2 tables with chi-square tests, or Fisher’s exact test in case the expected number under the null hypothesis is smaller than 1 in at least one of the cells. Number of AEs per individual will be compared using Poisson regression, or quasi-Poisson regression in case of overdispersion. EQ visual analogue score will be compared via linear regression in case it has a fairly symmetric distribution; otherwise we will use beta-regression. Normalization of neutrophils will be defined as first time to reach normal range of >2.0 ×10
^9^/l and for platelets the first time to reach >150 ×10
^9^/l and will be assessed by Cox model. For viraemia AUC and duration outcomes we will also perform the analysis with correction for day of illness (DOI). The time of fever clearance is defined by the first time after which all readings are <37.5°C in the following 48 hours.

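### Adverse events are counted over the whole study, but patients are observed daily only until discharge, so a difference in stay or early death between arms would bias the comparison

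*Protocol article*

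**What the plan says.** Under Secondary endpoints, the article lists the "number of adverse events per individual during the whole study course". No day window is attached. The serious adverse event (SAE) endpoint beside it is split into days 1–5 and days 6–30. The same list contains days in ICU, days in hospital and 30-day mortality.

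Under Statistical considerations, the comparison is: "Number of AEs per individual will be compared using Poisson regression, or quasi-Poisson regression in case of overdispersion". The sentence mentions neither observation time nor deaths.

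How events come to light is described in three sections:

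- In hospital (Data collection): "All patients will be reviewed daily until discharge", and "Standardized clinical information and a full blood count, biochemistry and research blood sampling will be performed at each visit".
- After discharge (Study treatment, monitoring and follow-ups): "All patients will be asked to come back for follow-up visits at day 30 and day 90 after fever onset". At those visits blood count and biochemistry are repeated and "patients will be asked about any newly emerging or persisting symptoms using a standardized questionnaire" (Data collection). Patients who miss a visit are telephoned.
- Recording (Safety review and monitoring): "All AEs occurring during the trial will be recorded in the CRF", whatever their relation to study drug, and "Clinical and Laboratory events will be graded according to Common Terminology Criteria for Adverse Events (CTCAE) definitions".

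**The concern.** The nominal counting period is the same for everyone, but the chance of finding an event within it is not. A transient laboratory abnormality is likely to be found while blood is drawn daily and likely to be missed between discharge and day 30. The number of days of close observation is set by discharge and death, and the trial hopes to influence both. The count can therefore mix two things: how often events happen, and how long each patient was watched.

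A model for overdispersed counts does not separate them. Quasi-Poisson widens the confidence interval and leaves the estimated ratio where it was.

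At stake is how a secondary safety comparison would be read. A lower count in the arm with shorter stays could be taken for better tolerability, and a higher count in the arm with longer stays for toxicity, when only observation differed.

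**Working it through.** The article gives no design figure for this endpoint, so there is none to reproduce. The only input taken from it is 80 patients per group (Statistical considerations). All other inputs are assumptions, chosen to show direction and range.

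**Assumptions, identical in both arms, so the true rate ratio is 1.00.** Recordable events occur at 0.5 per day on days 1–10 and 0.05 per day on days 11–90. All events in hospital are found. A fraction q of events after discharge is found, with q varied from 0 to 1. Mean stay is 5, 6 or 7 days.

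**Step 1: expected counts.** A survivor has 10 × 0.5 + 80 × 0.05 = 9 true events. With a stay of L days (L ≤ 10), the expected recorded count is E(L) = 0.5L + q(9 − 0.5L).

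| q | E(5) | E(6) | E(7) | E(5)/E(6) | E(5)/E(7) |
|---|---|---|---|---|---|
| 0 | 2.50 | 3.00 | 3.50 | 0.83 | 0.71 |
| 0.3 | 4.45 | 4.80 | 5.15 | 0.93 | 0.86 |
| 0.6 | 6.40 | 6.60 | 6.80 | 0.97 | 0.94 |
| 1 | 9.00 | 9.00 | 9.00 | 1.00 | 1.00 |

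**Step 2: simulation with the stated test.** Each scenario has 3000 trials with 80 per arm, individual stays drawn as 2 + Poisson(mean − 2), and a quasi-Poisson Wald test without an exposure term. The false-signal column is the chance that the shorter-stay arm shows significantly fewer events (nominal 2.5%).

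| q | Ratio, 5 v 6 days | False signal | Ratio, 5 v 7 days | False signal |
|---|---|---|---|---|
| 0 | 0.84 | 38% | 0.73 | 86% |
| 0.3 | 0.93 | 16% | 0.87 | 46% |
| 0.6 | 0.97 | 7% | 0.95 | 14% |
| 1 | 1.00 | 2% | 1.00 | 3% |

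As a control, equal mean stays (6 v 6) give a two-sided rejection rate of 4.3% to 5.3% across the four values of q. The test itself is sound; the distortion comes from unequal observation.

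**Step 3: early deaths alone.** Mean stays are equal at 6 days, and deaths fall evenly on days 2 to 7. With q = 0.3, mortality of 10% v 5% gives a ratio of 0.97, and 20% v 10% gives 0.94. With q = 1, 10% v 5% gives 0.96. A hand check of the last: a patient who dies has on average 4.5 × 0.5 = 2.25 events, so the ratio is (0.90 × 9 + 0.10 × 2.25)/(0.95 × 9 + 0.05 × 2.25) = 8.325/8.6625 = 0.96. Full detection after discharge removes the stay effect but not the death effect.

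**Step 4: would hospital days as an offset repair it?** Only at q = 0, where 5 v 6 days gives 1.00. At q = 0.3 the simulated ratio becomes 1.12 for 5 v 6 days and 1.22 for 5 v 7 days, so the shorter-stay arm now looks worse. By hand for 5 v 6: (4.45/5)/(4.80/6) = 0.89/0.80 = 1.11. Stay is itself a post-randomisation outcome, and dividing by it brings in a bias in the other direction.

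**Step 5: a common window.** With one fixed window, the same assessment schedule in both arms and time alive in the window as exposure, the ratio is 1.00 by construction under these assumptions.

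**The case against.** The case on the other side has several parts.

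- **An exposure term is ordinary analysis-plan content.** The article names a model family in one sentence and does not rule out an offset. This stands: its absence is not counted here as an error. What the article does fix is the counting period, and the most obvious offset, hospital days, would make matters worse (Step 4).
- **Surveillance after discharge is sparse, not absent.** This also stands, and it limits the size. A reader might take counts as proportional to hospital days and infer ratios of 6/7 = 0.86 or 5/7 = 0.71, with false-positive rates of up to about 90%. That requires nothing at all to be found after discharge and a constant event rate throughout the stay. The article provides two visits with blood tests and a symptom questionnaire, telephone contact for missed visits, and recording of all events. Background places severe manifestations mainly on illness days 4–6, so the days saved by earlier discharge are plausibly low-rate ones. A persisting abnormality also need not be counted afresh each day.
- **The effect may be real.** Safety review and monitoring foresees adverse events that keep patients in hospital beyond 5 days. Fewer events and a shorter stay can then be the same benefit. This stands; the raw count cannot tell the two apart.
- **Other safety measures exist.** A reader might infer that a signal such as neutropenia would be hidden, or that early deaths would make an arm look markedly safer. The article does not support either. It has a neutrophil-based stopping criterion and a time-to-normalisation endpoint for neutrophils, SAEs have fixed windows, 30-day mortality is its own endpoint, and the death effect in Step 3 is only about 3–6%.

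**Conclusion.** The concern holds as a conditional one. The whole-course count is open to bias if the arms differ in length of stay or early survival and detection after discharge is incomplete. The trial's hypothesis is that clinical outcomes improve, so a difference in stay is a situation to plan for. It is not a certainty, and the documents do not show that the shorter-stay arm will look safer.

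The size cannot be fixed from the article. Under the assumed rates and equal true risk, the ratio runs from about 0.84 to 1.00 for a mean stay one day shorter and from about 0.73 to 1.00 for two days shorter. The lower ends require that nothing is found after discharge. Doubling early mortality lowers the count by about 3–6%. This concerns one of many secondary endpoints and leaves the primary analysis untouched. It is a worthwhile, inexpensive improvement.

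**What to change.** Use the SAE windows for the adverse event count as well.

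- **Lead comparison:** the number of new or worsened adverse events per individual in days 1–5 after randomisation, by Poisson or quasi-Poisson regression with log(time alive in the window) as offset. State that the day-5 assessment applies to every participant. The 4-day intravenous course, the 5-day laboratory endpoints and the day-5 data for the first monitoring committee review all point that way. The explicit sentence on collection to day 5, however, sits in the paragraph on early drug stopping and prolonged stays.
- **Later events:** report days 6–30, and up to the end of study, separately. Split them into in-hospital and post-discharge events and show deaths alongside.
- **Whole-course count:** keep it as a descriptive summary.
- **Offset:** do not use hospital days.

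The cost is one sentence in the endpoint list and one term in the model, with no new data. The downside is that events after day 5 leave the lead comparison and must be read from the separate tables.

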### Exploratory endpoints

T/NK cell phenotype/activation over 5 days following randomization, 1 month and 3 monthsImmune cell gene signatures over 5 days following randomization and day 30Differential gene expression over 5 days following randomization and day 30

### Screening

Patients hospitalized to one of the study wards of the Hospital for Tropical Diseases (HTD), Ho Chi Minh City, Vietnam with clinically suspected dengue with warning signs/severe dengue will be identified and, if potentially eligible, approached by study staff. If patients agree to participate in the trial and provide the written consent/assent form, they will be screened for eligibility based on the criteria listed in the section above. Initial screening tests include baseline ferritin, creatinine, HBsAg and, in all female patients, a pregnancy test using a urine dipstick.

Potentially eligible patients who have baseline ferritin levels > 1000 ng/ml but ≤ 2000 ng/ml on admission will be invited to continue the screening phase of the trial which lasts for 3 days with daily ferritin testing. If the ferritin level rises to above 2000 ng/ml during this period, and all inclusion criteria are met, the patient will be recruited. If the ferritin remains below the 2000ng/ml threshold after 3 days, the screening phase will end and all study procedures will stop. Patients will also be excluded if their ferritin levels are below 1000ng/ml.

### Randomization

After confirmation of eligibility, including obtaining ICF for randomization phase, study doctors will perform randomization on the electronic data system (Ennov). Randomization will be minimization at 1:1 ratio and stratified according to the ward of recruitment. The system will assign a unique study ID and drug code for the patient. The assigned drug code will correspond to a sealed pre-packaged box containing 08 doses (bd dosing for 4 days) of either anakinra or visually matched placebo for adults or children. Drug appearance and administration schedules will be identical to maintain blinding amongst the attending physicians and nurses. Neither the patients nor the study assessors, including treating physicians, study doctors/nurses, know which group patients in.

### Study treatment, monitoring and follow-ups

Subsequent study procedures includes: daily study drug administration, daily clinical assessment, case Record Form (CRF) completion and blood sampling for a full blood count, biochemistry including ferritin, diagnostics, other inflammatory and vascular biomarkers and RNA extraction.

Participants will receive study treatment with Anakinra (Kineret) or visually matched placebo, given intravenously 200mg twice a day for 4 days (or 2mg/kg IV BD in children). Other general management of the febrile episode will be at the discretion of the treating physicians.

Study drugs will be stored in a refrigerator in a secure location at 2°C to 8°C and protected from light. All medication storage and administration will be regulated through the central pharmacy of the hospital to ensure good quality and control of medication handling. For the purpose of ambulatory use, Kineret may be kept at room temperature up to 25°C for a maximum of 72 hours.

All patients will be asked to come back for follow-up visits at day 30 and day 90 after fever onset. At these times, research blood samples will be taken for convalescent serology, immunology studies, a full blood count and biochemistry tests. Patients will be contacted 3 – 5 days prior to the follow-up visit to arrange an appropriate appointment date and time. Any patient who misses the follow-up visit will be contacted by phone either to reschedule the visit or to collect information if patients are unable to return in-person. 

### Unblinding

The Clinical Trials Pharmacist will hold the unblinded randomization list with details of the contents of each box of syringes. This list will be accessed only in the case of emergency unblinding, authorized by an investigator as per standard operating procedures. Emergency unblinding will only be performed in the case of an adverse event when the knowledge of the identity of the treatment will contribute to the treating physician’s ability to care for the patient.

